### Participants

Patients who meet the following criteria will be considered eligible: (1) age ≥18 years; (2) admission to the ICU specifically for sepsis, without any additional life-threatening injuries; (3) an expected duration of invasive mechanical ventilation of ≥72 h; (4) absence of S-AGI before enrollment, as no AGI standards have been met; (5) receipt of enteral nutrition via oral or nasogastric tube for 1 week or longer, as determined by the attending physician; and (6) provision of written informed consent by the patient or an authorized family member.

The diagnosis of sepsis is established based on the definition and diagnostic criteria outlined in the 2016 International Guidelines for the Management of Sepsis, which define sepsis as an imbalanced response to infection leading to dysfunction in vital organ systems, indicated by a sequential organ failure assessment (SOFA) score of ≥2. Accordingly, sepsis can be diagnosed when there is confirmed or suspected infection accompanied by a SOFA score of ≥2 (14).

Participants will be excluded if they meet any of the following criteria: (1) known or suspected acute gastrointestinal obstruction; (2) risk of gastrointestinal perforation; (3) history of peptic ulcer disease; (4) diagnosis of Crohn’s disease; (5) diagnosis of Ogilvie syndrome; (6) acute diverticulitis; (7) presence of infiltrative gastrointestinal tumors; (8) recurrent or advanced ovarian cancer with peritoneal metastasis; (9) history of abdominal trauma with potential risk of gastrointestinal perforation; (10) any other primary gastrointestinal diseases; (11) myocardial infarction within the past 6 months with evident clinical manifestations related to the congestive cardiovascular system and QT interval ≥500 ms; (12) family members opting for conservative treatment measures on behalf of the patient; (13) known pregnancy or breastfeeding; (14) severe liver cirrhosis classified as Child-Pugh grade C; (15) history of one or more life-threatening events; (16) participation in other clinical trials within the previous month, including ongoing trials, and (17) post-cardiac pacemaker surgery or presence of metal implants/prostheses in the body.

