### Outcomes

#### Primary outcome

The primary outcome is the 10-day incidence rate of S-AGI.

The occurrence of S-AGI is defined as the development of gastrointestinal symptoms in a patient who had no symptoms at baseline, with an AGI grade of 1 to 4 at the time of assessment.

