### Sample size

A parallel-design, randomized controlled trial methodology will be employed in the trial, with the primary outcome measure being the incidence of S-AGI. Based on clinical observations, the estimated incidence of S-AGI in the conventional treatment group is 70%. It is anticipated that electroacupuncture can potentially reduce the occurrence rate of S-AGI to 50%. With a significance level (*α*) of 0.05 and a power of 0.8, the sample size calculation yielded 94 participants per group. To account for potential loss to follow-up, we plan to include a total of 200 sepsis patients, with 100 patients allocated to each group. To account for uncertainties and maintain adequate power if the effect size is smaller than expected, sample sizes were also calculated as 163 participants per group for a 15% effect size and 356 participants per group for a 10% effect size.

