### Statistical analysis

Statistical analysis will be performed using the SPSS software (version 29.0). For continuous data, a normality test will initially be conducted to assess distribution characteristics. If the data exhibit a normal distribution, descriptive statistics such as mean ± standard deviation (*SD*) will be used, and hypothesis testing will be carried out using a *t*-test. Conversely, if the data do not follow a normal distribution, descriptive statistics such as median and interquartile range (*IQR*) will be employed, and hypothesis testing will be performed using the *Mann–Whitney U* test. Categorical data will be described in terms of frequencies and percentages, with the chi-squared test used for hypothesis testing. The significance level for this study will be set at *α* = 0.05, with statistical significance defined as a *p*-value of <0.05. This trial includes 13 key secondary outcome indicators, covering both clinical and prognostic measures. To address multiplicity and control type I error, we applied the *Bonferroni* correction at both levels.

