## Discussion

In our clinical research proposal, we focus on sepsis patients who require invasive mechanical ventilation. Invasive mechanical ventilation is common among sepsis patients admitted to the ICU, with studies indicating that approximately 21.38%–51.67% of sepsis cases necessitate this intervention (25, 26).

According to our clinical observations, several factors contribute to the increased susceptibility of mechanically ventilated sepsis patients to S-AGI. First, these individuals often exhibit a more severe clinical status, characterized by hypotension and multi-organ dysfunction that can compromise splanchnic blood flow and gastrointestinal integrity. Second, the use of sedatives and analgesics during mechanical ventilation can diminish gastrointestinal motility and impair the protective mucosal barrier, further predisposing patients to S-AGI. Moreover, the inflammatory response associated with sepsis can directly disrupt gut barrier function. A previous study reported that clinical ill patients who received preventive treatment for AGI exhibited a notably higher intake of the nutrient solution and a considerably shorter duration of invasive mechanical ventilation compared to those without any preventive measures (5).

S-AGI significantly impacts the prognosis of sepsis patients, increasing the risk of complications and mortality. Currently, there are no effective preventive strategies for S-AGI, underscoring the need for alternative interventions. Electroacupuncture has shown potential in preventing S-AGI; however, high-quality evidence from RCTs remains scarce. Therefore, it is crucial to conduct an RCT to establish the efficacy of electroacupuncture in preventing S-AGI, providing much-needed evidence to guide clinical practice and improve outcomes in sepsis patients.

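### The primary S-AGI comparison is an unadjusted chi-squared test; pre-specified adjustment for baseline SOFA would improve precision at little cost, but the planned test is not an error

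*Protocol article*

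**What the plan says.** All references are to the protocol article.

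- **Primary outcome:** "The primary outcome is the 10-day incidence rate of S-AGI". Each patient either develops S-AGI or does not.
- **Statistical analysis:** "Categorical data will be described in terms of frequencies and percentages, with the chi-squared test used for hypothesis testing". This general rule covers the primary outcome. No covariate or adjusted model is mentioned.
- **Sample size:** 70% under conventional treatment against 50% with electroacupuncture. At a significance level "of 0.05 and a power of 0.8, the sample size calculation yielded 94 participants per group"; 100 per group are to be enrolled.
- **Randomization:** 1:1 allocation from a computer-generated sequence in sealed envelopes. No stratification factor is described.
- **Participants:** sepsis is diagnosed on "confirmed or suspected infection accompanied by a SOFA score of ≥2", so SOFA has to be assessed before entry.
- **Table 1:** SOFA is not listed by name; there is only a general row for baseline characteristics.
- **Discussion:** ventilated sepsis patients are said often to have a "more severe clinical status, characterized by hypotension and multi-organ dysfunction that can compromise splanchnic blood flow and gastrointestinal integrity". No figure links severity to S-AGI.

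**The concern.** A severity measure has to be assessed for every patient before randomisation, and the authors regard severity as relevant to gut injury. Neither the allocation nor the primary test, as described, makes use of it. The Discussion relies on clear eligibility criteria for baseline consistency, but a SOFA floor restricts who enters and does not balance the arms.

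Two things are at stake. If SOFA predicts S-AGI, adjustment would give more power from the same 200 patients. And in the one randomisation that is actually carried out, a chance severity difference stays in the crude estimate. Adjusting only after such a difference has been seen would be post hoc, so the choice has to be made in advance.

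**Working it through.** **1. Inputs.** From Sample size: 70% and 50%, alpha 0.05, power 0.80, 94 per group required, 100 enrolled. Sidedness is not stated. Two-sided is assumed, because a one-sided test would need only 74 per group.

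**2. Reproducing the plan's figure.** With mean risk 0.60 and pooled variance under the null:

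n = [1.960·√(2·0.6·0.4) + 0.842·√(0.7·0.3 + 0.5·0.5)]² / 0.20² = (1.358 + 0.571)² / 0.04 = 93.0.

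With pooled variance in both terms, n = 94.2. The stated 94 agrees with an unadjusted two-proportion test.

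**3. Power of the planned test.** Power = Φ[(0.20·√n - 1.358) / 0.678].

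- n = 94: Φ(0.857) = 80.4%.
- n = 100: Φ(0.947) = 82.8%.

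**4. How often severity is imbalanced.** With 100 per arm, the between-arm difference in a standardised score has SD √(2/100) = 0.141. The chance that it exceeds 0.2 SD in either direction is 2·[1 - Φ(0.2/0.141)] = 15.7%. Simulation gave about 15-16%.

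**5. Gain from adjustment (simulation).** Model: logit P(S-AGI) = intercept for the arm + b·X, with X a standard normal severity score. The intercepts are set so that the overall risks are 70% and 50%. There were 4,000 trials per setting. The odds ratio per SD, exp(b), is an assumption and is varied from 1.0 to 3.0. Adjusted power is that of the likelihood-ratio test for arm in a logistic model containing X. The variance ratio compares the standardised risk difference with the crude one. The last column is the simulated change in the crude risk difference per SD of imbalance, multiplied by 0.2.

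100 per group:

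| OR per SD | Chi-squared power | Adjusted power | Gain (points) | Variance ratio | Shift at 0.2 SD (points) |
|---|---|---|---|---|---|
| 1.0 | 83.2% | 83.2% | 0.0 | 1.007 | about 0 |
| 1.3 | 83.7% | 84.0% | 0.3 | 0.985 | 0.063·0.2 = 1.3 |
| 1.5 | 83.3% | 84.7% | 1.4 | 0.968 | 0.090·0.2 = 1.8 |
| 2.0 | 83.2% | 86.4% | 3.2 | 0.918 | 0.142·0.2 = 2.8 |
| 2.5 | 83.7% | 88.2% | 4.5 | 0.852 | 0.192·0.2 = 3.8 |
| 3.0 | 82.5% | 89.4% | 6.9 | 0.823 | 0.203·0.2 = 4.1 |

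The Monte Carlo standard error of each power figure is about √(0.83·0.17/4000) = 0.6 points.

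At 94 per group, power goes from 80.3% to 81.9% at OR 1.5, from 80.1% to 84.3% at 2.0 and from 80.6% to 88.0% at 3.0.

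**6. Consistency check.** A variance ratio of 0.918 multiplies the expected z-statistic by 1/√0.918 = 1.044. At OR 2.0 the crude value is 1.960 + 0.962 = 2.922. This becomes 3.050, and Φ(3.050 - 1.960) = 86.2%, close to the simulated 86.4%. The same reduction corresponds to a crude analysis of 200/0.918 = 218 patients.

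**7. Validity of both analyses.** At 100 per group the mean crude risk difference was -0.199 to -0.201 against a true -0.200. With 70% in both arms, the type I error was 4.7% to 5.6% for chi-squared and 4.7% to 5.4% for the adjusted test.

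**The case against.** The strongest reply is that nothing is wrong with the plan. A chi-squared test on a binary outcome after 1:1 randomisation is valid, its standard error already allows for chance imbalance, and it is the analysis on which the sample size rests. All of this stands. A reader might infer that the primary result would be biased or the trial underpowered for its stated effect. Steps 3 and 7 show neither.

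The second reply concerns the Discussion. A reader might take it as showing that SOFA is prognostic within this trial. It explains why ventilated sepsis patients as a group are susceptible. Everyone enrolled has SOFA of at least 2, is expected to be ventilated for at least 72 hours and is free of AGI at entry, so the restricted range may weaken any association. This also stands, which is why the range starts at an odds ratio of 1.0. Nothing in the documents supports age as a covariate.

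Third, a reader might infer that SOFA is already in the dataset. Eligibility shows only that the threshold was assessed, and Table 1 does not name the score.

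Finally, an analysis plan that is not shown may add an adjusted analysis. That is possible, but the article does more than leave the matter open: it names the test. The replies limit the size of the point and the confidence in it. They do not remove it, since the expected loss from adjusting is negligible even if SOFA predicts nothing.

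**Conclusion.** The point holds as a recommendation on efficiency and precision. It is well supported that the stated primary test is unadjusted, that no severity stratification is described, and that SOFA must be assessed at entry. The size of the benefit is uncertain because it rests on an association that the documents do not give. At 100 per group the gain in power is nil at an odds ratio of 1.0 per SD, 1.4 points at 1.5, about 3 at 2.0 and about 7 at 3.0, with the variance changing from about +1% to -18%. A 0.2 SD imbalance would move the crude estimate by about 2 to 4 points, against a planned effect of 20, at odds ratios of 1.5 to 3.0. That movement is ordinary sampling variation, part of which adjustment can remove. All these figures assume one normally distributed score that acts linearly on the log-odds.

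**What to change.** Before the statisticians are unblinded:

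1. Specify the primary analysis as logistic regression of day-10 S-AGI on arm and baseline SOFA as a numeric score; age is optional. Report it as a standardised (marginal) risk difference with 95% CI and p-value, which stays on the scale of the planned 70% against 50%.
2. Keep the chi-squared test as a supporting analysis, and state that the adjusted result is the one that decides.
3. Name the numeric SOFA score as a baseline item on the case report form and in Table 1.

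The cost is a few sentences in the plan, a few lines of code and, if the score is not yet captured, one form field filled from the eligibility assessment. The sample size need not change. The downside is slightly more analysis work and about 1% more variance if SOFA turns out not to be prognostic.

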## Abstract

**Background:**

Septic acute gastrointestinal injury (S-AGI) plays a vital role in the initiation and progression of sepsis. Electroacupuncture (EA) is utilized for the treatment and prevention of S-AGI due to its positive impact on gastrointestinal function. However, there is a lack of rigorous trials examining the effectiveness and safety of EA in this context. Thus, a randomized controlled trial (RCT) at a single center has been designed to thoroughly assess the efficacy and safety of EA as an adjunctive therapy for preventing the incidence of S-AGI in patients with sepsis.

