Growing evidence suggests that acupuncture alone, or in combination with Western medicine, can improve the clinical prognosis of S-AGI, including significant reductions in 28-day mortality and improvements in AGI grade and gastrointestinal function. A retrospective propensity score-matched cohort study conducted by our team evaluating the effects of electroacupuncture (EA) at “Zusanli” (ST36) and “Guanyuan” (RN4) on S-AGI demonstrated a 54% reduction in 28-day mortality among patients who received EA (9). Furthermore, in our recent randomized controlled trial (RCT), electroacupuncture combined with standard treatment improved clinical outcomes by regulating the immune system compared to standard treatment alone (10). Meng et al. conducted an RCT and reported that patients with S-AGI exhibited significant improvements in AGI grade and gastrointestinal function when acupuncture was used as an adjunctive therapy (11). However, findings regarding its impact on mortality have been inconsistent. Meng et al. found that the use of acupuncture as an adjuvant therapy decreased 28-day mortality in patients with S-AGI compared to standard treatment alone (11). However, another RCT reported no significant effect on mortality (12). Therefore, studies with a larger sample size are needed to clarify the effects of acupuncture on both gastrointestinal function and mortality in patients with sepsis.

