#### Secondary outcomes

Secondary outcomes consist mainly of 16 indicators. It includes clinical and prognostic indicators (key secondary outcomes) and biochemical indicators (exploratory outcomes).

Clinical indicators include the following: (1) Average classification of the AGI grade, (2) gastric retention volume within 1 day, (3) abdominal circumference, (4) abdominal pressure, (5) frequency of bowel sounds, (6) number of days tolerating the daily feeding target, (7) proportion of patients receiving erythromycin and/or metoclopramide for feeding intolerance management, and (8) proportion of patients receiving one or more rectal laxatives for constipation management.

Biochemical indicators include the following: (1) Plasma concentration of motilin, (2) plasma concentration of gastrin, and (3) plasma concentration of prealbumin.

Prognostic indicators include the following: (1) Incidence of S-persistent inflammation, immunosuppression, and catabolism syndrome (PICS), (2) duration of invasive mechanical ventilation in days, (3) ICU length of stay in days, (4) mortality rate at day 7, and (5) mortality rate at day 28.

To assess gastrointestinal function, the AGI grade will be used (4). The AGI grade is widely used to evaluate gastrointestinal injury in patients with acute critical illness (4, 18). Evidence has shown that the AGI grading system is useful for determining the severity of gastrointestinal dysfunction/failure in sepsis (19). The specific criteria for AGI grading are provided in Supplementary File S1.

At baseline and on days 4, 8, and 10, AGI grading will be assessed, and gastric retention volume, abdominal circumference, abdominal pressure, and frequency of abdominal bowel sounds will be measured. The specific measurement procedures for these clinical indicators are detailed in Supplementary File S1. We will also record the gastric retention volume over the previous 24 h, the actual caloric intake from enteral nutrition, and any special treatments related to S-AGI, including the use of erythromycin and/or metoclopramide for feeding intolerance management or the use of one or more rectal laxatives for constipation management. In addition, we will collect venous blood samples from patients at baseline and on days 4, 8, and 10 to measure the plasma concentration of motilin and gastrin, which serve as indicators of gastrointestinal motility.

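### Day-7 and day-28 deaths sit inside the Bonferroni-corrected secondary family, so the only between-arm test of mortality described makes an excess of deaths on electroacupuncture harder to flag

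*Protocol article*

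**What the plan says.** The Abstract (Background) says the trial is designed to "thoroughly assess the efficacy and safety of EA as an adjunctive therapy". The Background and rationale section calls earlier mortality findings inconsistent and concludes that "studies with a larger sample size are needed to clarify the effects of acupuncture on both gastrointestinal function and mortality in patients with sepsis".

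The Secondary outcomes section lists, among the prognostic indicators, "4) mortality rate at day 7, and (5) mortality rate at day 28". It labels the clinical and prognostic indicators as key secondary outcomes and the biochemical ones as exploratory. There are 8 clinical and 5 prognostic indicators.

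The Statistical analysis section describes categorical data by frequencies and percentages, "with the chi-squared test used for hypothesis testing", "with statistical significance defined as a *p*-value of <0.05". It then says: "This trial includes 13 key secondary outcome indicators, covering both clinical and prognostic measures". The correction follows: "To address multiplicity and control type I error, we applied the *Bonferroni* correction at both levels". No divisor is given, and mortality is not exempted.

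On safety, the Safety assessment section has adverse events recorded and serious adverse events in either group sent to an independent ethics committee. The Data management section gives the data monitoring committee a remit over data quality.

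**The concern.** A Bonferroni correction protects against false positive claims across a family of outcomes. That protection is wanted when the claim is benefit. When the question is whether more patients die on the experimental arm, a false negative is the costlier error, and the correction makes it more likely.

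This is a rule that the article states, not a detail left to a fuller document: mortality is a key secondary outcome, and the key secondary outcomes are corrected. An analysis plan that followed the rule would inherit it. At stake is how a sizeable excess of deaths in ventilated sepsis patients would be classified: a difference that is significant at 0.05 could be recorded as non-significant because the trial also measured abdominal circumference and bowel sounds.

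**Working it through.** **Inputs.** From the Sample size section: 100 per arm, overall alpha 0.05. From the Secondary outcomes and Statistical analysis sections: 13 key secondary outcomes (8 + 5), chi-squared test. Control mortality is an assumption, because the article gives no planning rate for deaths. I used its background figures: 17% and 26% (hospital mortality, sepsis and severe sepsis) and 30% (the Chinese case fatality figure is given as above 30%).

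**The plan's own figure first.** For 70% against 50%, two-sided 0.05, power 0.80, pooled variance:

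n = [1.96·√(2·0.6·0.4) + 0.842·√(0.7·0.3 + 0.5·0.5)]² / 0.20² = 93.0 per arm, against 94 stated. The same formula gives 163 and 356 for the 15- and 10-point effects, as stated. A one-sided calculation gives 74, so the plan's figures are two-sided.

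**Corrected threshold.** The divisor is not stated. With all 13 outcomes in one family, 0.05/13 = 0.00385. If the 5 prognostic outcomes are corrected on their own, 0.05/5 = 0.01.

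**Chance of missing a true excess of deaths.** Exact enumeration of two independent binomials, 100 each. A result counts as detected if the uncorrected Pearson chi-squared test is significant and electroacupuncture has more deaths. Entries are the percentage missed at control mortality 17% / 26% / 30%.

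| True excess | 0.05/13 | 0.05/5 | 0.05 |
|---|---|---|---|
| 10 points | 89 / 91 / 92 | 80 / 85 / 86 | 60 / 66 / 68 |
| 15 points | 66.5 / 74 / 76 | 53 / 63 / 64 | 30 / 38 / 41 |
| 20 points | 37 / 47 / 50 | 25 / 35 / 37 | 10 / 16 / 17 |

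The correction does most damage at 15 points, where the chance of a miss rises from 30–41% to about 67–76%.

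**Smallest observed excess that reaches significance.** At 0.05/13: 17 against 35 deaths per 100, 26 against 46, or 30 against 51, that is, 18 to 21 more deaths. At 0.05: 17 against 29, 26 against 39, or 30 against 44, that is, 12 to 14 more.

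**One worked result.** Suppose 30 control deaths and 45 electroacupuncture deaths. The pooled proportion is 0.375, and chi-squared = 0.15² / (2·0.375·0.625/100) = 4.80, p = 0.028. That is non-significant at both 0.00385 and 0.01. The unadjusted 95% confidence interval for the risk difference is 0.15 ± 1.96·√(0.30·0.70/100 + 0.45·0.55/100) = 1.7 to 28.3 points, which excludes zero.

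**Precision of the interval.** With 30% mortality in both arms, the half-width is 1.96·√(2·0.3·0.7/100) = 0.127, about 13 points.

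**The case against.** The strongest reply has four parts.

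1. *Deaths will be visible.* The Statistical analysis section has categorical outcomes described by frequency and percentage, so an excess of 15 to 20 deaths per 100 would be on the page. Serious adverse events also go to an ethics committee. This stands: it would be wrong to say that the test is the only view of deaths. But no unadjusted comparison of deaths by arm is described in either place.

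2. *The article does not equate non-significance with safety.* A reader might infer that a null mortality test would be presented as evidence that electroacupuncture is safe. The documents do not support that. Mortality is filed under prognosis, safety has its own section built on adverse events, and the Background treats conflicting mortality results as a reason for larger studies. The point concerns the stated threshold, not an announced conclusion.

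3. *The trial's size, not the correction, limits it at small excesses.* This holds at 10 points, where 60–68% would be missed with no correction at all. A reader might also infer that excesses up to 20 points would usually be missed. They would not: at 0.05/13 a 20-point excess is detected 50–63% of the time, and at 0.05/5 63–75%. The figures above are for 28-day mortality. Day-7 mortality cannot be higher; at an assumed 10%, a 20-point excess is detected about 76% of the time at 0.05/13.

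4. *Confidence intervals and safety tables are commonly left to the analysis plan.* Agreed, and their absence from an article is not the finding. The finding is that deaths are placed under the correction, which the article does explicitly.

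**Conclusion.** The concern holds in a limited form. Both mortality outcomes are inside the corrected family, and the corrected chi-squared test is the only between-arm inference on deaths described. The clearest consequence is for a true excess of about 15 points: missed about 67–76% of the time at 0.05/13, or 53–64% at 0.05/5, against 30–41% at 0.05. More misses than detections are therefore expected under either divisor. At 10 points the correction worsens a weakness that is already there; at 20 points detection is even or better.

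These figures assume 100 evaluable patients per arm, control 28-day mortality of 17–30% taken from background statements, and a two-sided uncorrected Pearson test. The primary analysis is unaffected.

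**What to change.** In the Statistical analysis section:

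- Keep the Bonferroni threshold for any claim that electroacupuncture reduces mortality.
- For assessing harm, take day-7 and day-28 mortality out of the corrected family. Report each as a risk difference (electroacupuncture minus control) with an unadjusted 95% confidence interval.
- State that a non-significant mortality test will not be reported as absence of harm.

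The cost is a few sentences and two intervals, with no extra patients or data. The small downside is that the interval will be wide (the ±13 points above), so the trial cannot offer strong reassurance on deaths. The corrected test could not offer it either; the interval makes that plain.

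### The multiplicity rule for the 13 key secondary outcomes is indeterminate: no levels, divisor or threshold are given, so the claimed type I error control cannot be verified

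*Protocol article*

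**What the plan says.** Three parts of the protocol article bear on this.

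- **Statistical analysis.** The level for the study is 0.05, "with statistical significance defined as a *p*-value of <0.05". The sentence is not limited to the primary outcome. Then: "This trial includes 13 key secondary outcome indicators, covering both clinical and prognostic measures". The paragraph closes with "To address multiplicity and control type I error, we applied the *Bonferroni* correction at both levels". No level is named, and neither a divisor nor an adjusted threshold is given.
- **Secondary outcomes.** The 16 indicators are split by role: "It includes clinical and prognostic indicators (key secondary outcomes) and biochemical indicators (exploratory outcomes"). The lists contain 8 clinical, 5 prognostic and 3 biochemical indicators. Five of the clinical ones are measured repeatedly: "At baseline and on days 4, 8, and 10, AGI grading will be assessed, and gastric retention volume, abdominal circumference, abdominal pressure", and likewise "frequency of abdominal bowel sounds will be measured". The AGI grade outcome is listed as an average. For the other four, no analysis day or summary is named.
- **Sample size.** The single primary outcome, S-AGI incidence, is sized at 70% versus 50% with alpha 0.05 and power 0.8, giving 94 per group.

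**The concern.** A Bonferroni rule is defined by its family. Once the family is known, the divisor and the threshold follow. Here the rule is stated and credited with controlling type I error, but the family is left open. The word for the two levels could point back to the clinical and prognostic groups in the sentence before it, or to the primary and secondary tiers. An unqualified p<0.05 in the same paragraph adds to the doubt.

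The threshold decides which secondary findings, mortality and days of ventilation among them, may be claimed. If it is not fixed beforehand, the reading can be chosen after the p-values are known, and no reader can check the claim of control.

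**Working it through.** **Inputs.** Overall alpha 0.05 and 13 key secondary outcomes (Statistical analysis). Split 8 clinical + 5 prognostic = 13 (Secondary outcomes), so the count of 13 is right. Primary outcome 70% versus 50%, alpha 0.05, power 0.8, 94 per group (Sample size).

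**Step 1: which alpha the primary test uses.** The pooled-variance formula for two proportions, two-sided, without continuity correction, is

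n = [1.96·√(2·0.6·0.4) + 0.8416·√(0.7·0.3 + 0.5·0.5)]² / 0.2² = (1.358 + 0.571)² / 0.04 ≈ 93 per group.

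The plan states 94. The same formula gives 163 for 70% versus 55% and 356 for 70% versus 60%, exactly the article's two alternative figures. A one-sided test would need only 74. The trial is therefore sized with the full two-sided 0.05 on the primary outcome.

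**Step 2: thresholds for the secondary outcomes.**

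| Reading | Threshold per outcome | Error over the 13, upper bound | Error over the 13, independent tests |
|---|---|---|---|
| One family of 13 | 0.05/13 = 0.00385 | 13 × 0.00385 = 0.05 | 1 − (1 − 0.00385)^13 = 0.049 |
| Clinical (8) and prognostic (5) separately | 0.05/8 = 0.00625; 0.05/5 = 0.01 | 0.05 + 0.05 = 0.10 | 1 − (0.99375)^8 × (0.99)^5 = 0.096 |

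Both rows assume one test per outcome.

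A third reading takes the levels as primary and secondary. With one primary outcome, Bonferroni within each level leaves 0.05 for the primary and 0.05/13 for each secondary. For the secondary outcomes this is the first row again, and it agrees with the sample size.

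**Step 3: what the difference decides.** The two-family threshold is 13/8 = 1.6 times the one-family threshold for a clinical outcome and 13/5 = 2.6 times for a prognostic one. A clinical result at p = 0.005 passes 0.00625 and fails 0.00385. A prognostic result at p = 0.008 passes 0.01 and fails 0.00385.

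**The case against.** The strongest defence is that nothing stated is strictly false. Thirteen is the correct count, and 0.05/13 does hold 5% with one test per outcome. An overall alpha of 0.05 is what Bonferroni divides, or what adjusted p-values are compared with, so the two sentences can coexist. Two separate families are a legitimate choice, and the article nowhere promises 5% across all 13. An analysis plan that is not shown may name the analysis day. All of this stands. It does not settle which threshold applies, because the article states a rule and that rule has more than one meaning.

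Stronger conclusions are tempting, and the article does not support them:

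- *That type I error control fails.* It holds under the one-family reading. What can be said is that it cannot be verified.
- *That each measurement day is a separate test.* Five outcomes on three days plus eight others would make 23 tests. At 0.05/13 that gives at most 8.8% (8.5% if independent; 6.6% in a simulation with an assumed between-day correlation of 0.9). With AGI grade as one summary, 21 tests would give at most 21 × 0.00385 = 8.1%. The article gives days of measurement, not a plan to test each day, so these figures are conditional.
- *That the 13 are tested unadjusted at 0.05.* The resulting 1 − 0.95^13 = 49% ignores the Bonferroni sentence.
- *That the primary alpha is split.* At an assumed 0.025, power with 100 per group would drop from 82.8% to 74.5%. Nothing in the article halves the alpha, and the sample size uses all of it.

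**Conclusion.** The point holds as one of indeterminacy. The threshold for the 13 key secondary outcomes may be 0.00385, or 0.00625 and 0.01, with error over the 13 of at most 5% or at most 10% respectively. Both bounds assume one test per outcome; the 9.6% figure also assumes independence. The primary analysis is unaffected if it is tested at 0.05, as the sample size implies. What is at stake is which secondary results can be claimed, and whether that was fixed before the data were seen.

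**What to change.** Replace the closing sentences of the Statistical analysis section with a rule that can be applied without interpretation:

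1. The single primary outcome is tested at two-sided 0.05, as in the sample size calculation. The p<0.05 statement applies to this test only.
2. The 13 key secondary outcomes form one family, tested by Holm's procedure at overall 0.05. The smallest p-value is compared with 0.05/13 = 0.00385, the next with 0.05/12 = 0.00417, and so on, stopping at the first failure.
3. Each of the 13 has one test. For those measured on days 4, 8 and 10, a day or a summary is named.
4. Other days and the three biochemical outcomes are reported descriptively.

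The cost is a few sentences, with no change to sample size, visits or data. On the same family, Holm is valid under any dependence and never less powerful than Bonferroni. There are two small drawbacks: matching simultaneous confidence intervals are less simple, and the starting threshold is stricter than with two separate families. If the sponsor prefers two families, that is defensible, provided it is stated together with the 10% bound over the 13.

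Testing the secondary outcomes only if the primary succeeds is optional. Without it, the primary and the secondary family are each held at 5%, so at most 10% jointly. With it, the joint rate is 5%, but no confirmatory secondary claim is possible if the primary fails.
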